## Abstract

**Background:**

To support advanced cancer patients and their oncologists in therapeutic decisions, we aim to develop a decision aid (DA) in a multiphased, bicentric study. The DA aims to help patients to better understand risks and benefits of the available treatment options including the options of standard palliative care or cancer-specific treatment (ie, off-label drug use within an individual treatment plan).

**Objective:**

This study protocol outlines the development and testing of the DA in a pre-post study targeting a heterogeneous population of advanced cancer patients.

**Methods:**

In the first step, we will assess patients’ information and decisional needs as well as the views of the health care providers regarding the content and implementation of the DA. Through a scoping review, we aim to analyze specific characteristics of the decision-making process and to specify the treatment options, outcomes, and probabilities. An interdisciplinary research group of experts will develop and review the DA. In the second step, testing of the DA (design and field testing) with patients and oncologists will be conducted. As a last step, we will run a pre-post design study with 70 doctor-patient encounters to assess improvements on the primary study outcome: patients’ level of decisional conflict. In addition, the user acceptance of all involved parties will be tested.

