### Design and Settings

First, patients will be recruited in a baseline phase lasting 4 months to observe usual care without using the DA. It means that oncologists will inform patients about further treatment options for cancer-specific therapy, side effects, and potential benefit, but they will not explicitly address that best supportive care would also be an option and will not use a decision support tool for eliciting patient preferences and assisting in decision making. The baseline phase will be followed by an intervention phase lasting 6 months. Oncologists and patients will use the DA in the same situation (change of treatment needs to be discussed with the patient because of disease progression, treatment toxicity, or other reasons). A minimum of 40 doctor-patient encounters will be included in the 4-month baseline, and 40 doctor-patient encounters will also be included in the 6-month DA intervention phase. The whole sample will encompass 80 doctor-patient encounters. The planned sample size is largely determined by the feasibility of recruiting patients within the available project duration.

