### Sample Characteristics

Patients will be recruited at participating study sites (Jena, Heidelberg) in inpatient and outpatient settings. Patients will be identified by a study nurse via the electronic health record of patients scheduled in the outpatient or inpatient clinic and approached for participation if they fulfill the inclusion criteria.

We will include adult patients with incurable, stage IV disease (prostate, breast, pancreatic, stomach, or colorectal cancer) in an advanced treatment stage (prognosis <12 months or standard palliative care only is considered). The patient must have an adequate level of the German language to complete the questionnaire and is willing and able to give informed consent for participation in the study.

We will exclude patients from the study who are already under standard palliative care only, are cognitively impaired, have extreme anxiety or distress, or have a severe comorbid illness, excluding antitumor treatment as assessed by the treating oncologist.

The influence of implicit bias will be reduced by recruitment of patients both in Heidelberg and Jena. In addition, the use of a trained study nurse at both sites will reduce implicit bias in recruitment. Drop-out reasons will be documented.

Oncologists will be recruited from the participating study sites (Jena, Heidelberg). They will be identified by a study nurse and invited to participate in the study via phone. We will include oncologists with different levels of working experience and of varying ages. The oncologists who participated in the development of the DA will be excluded from participation in the study.

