### Data Analysis

Analyses will be performed using SPSS v.20.0. A descriptive analysis of the sample will be performed. According to the level of variables, means, SDs, medians, minimum and maximum, and absolute or relative frequencies will be reported.

Clinically significant decisional conflict will be calculated and defined by a score of ≥25/100 on the Decision Conflict Scale, which is the most commonly used threshold to distinguish a harmful level of decisional conflict [62-64].

We will compare primary and exploratory outcome measures between the 2 patient groups (baseline and intervention) using Student *t* tests or analysis of variance. Parametric or nonparametric statistics (depending on the distribution of the data) will be used for the analysis of the patient groups from the baseline and intervention phases.

We will compare clinical confounders (time of integration of specialized palliative services into care; aggressiveness of therapy [anticancer treatment <14 days before death and place of death]) between the 2 patient groups (baseline and intervention) by comparing mean values. Measures of variability (SD) will be calculated.

Given the practice-based character and the small sample size of the study, we refrain from extensive measurement and multivariate analysis of mediators and moderators of the intervention effects. For the latter reason, we do not plan to use multiple imputation of missing values. Missing values will be handled by allowing a maximum of 35% missing in the calculation of scale scores.

*P* values of the corresponding statistical tests comparing treatment groups (ie, 2-sample *t* tests for continuous variables and chi-square tests for categorical data) will be given. Statistical significance will be assessed at the level of α=.05 (two-sided).

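### The abstract gives 70 doctor-patient encounters for the pre-post study and the methods give 80, and nothing in the article links the two totals

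*Protocol article*

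**What the plan says.** The Methods paragraph of the abstract announces the last step of the project in these words: "we will run a pre-post design study with 70 doctor-patient encounters to assess improvements on the primary study outcome".

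The Design and Settings section of the main text sets the size phase by phase. For baseline: "A minimum of 40 doctor-patient encounters will be included in the 4-month baseline". For the intervention phase: "40 doctor-patient encounters will also be included in the 6-month DA intervention phase". It then gives the total: "The whole sample will encompass 80 doctor-patient encounters". The reason offered is practical: "The planned sample size is largely determined by the feasibility of recruiting patients within the available project duration". The article gives no effect size, standard deviation or power.

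Three other places bear on the point:

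- Data Analysis describes the comparison as one between two groups of patients, baseline and intervention, using a t test or analysis of variance at a two-sided 5% level.
- Sample Characteristics deals with loss only by saying "Drop-out reasons will be documented"; no rate is given.
- The Overview of the methods and the section introducing the pre-post study both list the estimation of recruitment and retention among the objectives of this phase.

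**The concern.** Two totals for one study cannot both be the target. A reader would look for a bridge between them, such as an allowance for attrition or a distinction between encounters enrolled and encounters analysed. The article contains none.

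The number matters because recruitment is itself something this phase sets out to assess. If the study closed with 70 encounters, it would be complete by the abstract and 10 short by the methods. Nor can a reader settle the matter by calculation. The size rests on feasibility, so no sample size formula exists from which the intended figure could be recovered. The stated total is the only anchor, and the abstract, where the divergent figure stands, is the part of the article most widely read.

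**Working it through.** **Inputs from the article**

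- Total in the abstract: 70.
- Baseline phase: at least 40. Intervention phase: 40. Total: 80 (all from Design and Settings).
- Two independent groups, two-sided α = 0.05 (Data Analysis).

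**Inputs that are assumptions**

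- How 70 would divide between phases. The abstract gives no split, so 35 + 35 and 40 + 30 are both shown.
- Differences of 0.5 and 0.6 SD, and SDs of 15, 20 and 25 points on the Decision Conflict Scale. The article gives none of these.
- Independent encounters with a common SD.

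**Step 1: reproduce the totals.** 40 + 40 = 80, so the total in Design and Settings is reproduced exactly. The abstract's 70 is not. The gap is 80 − 70 = 10, and 10/80 = 12.5%. A loss of 12.5% would turn 80 into 70, but that rate is worked back from the mismatch and appears nowhere in the article. Because the baseline figure is worded as a minimum, 80 is if anything a lower bound, and 70 lies below it.

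**Step 2: precision.** In SD units, the half-width of the 95% confidence interval for the difference in means is t(0.975, n₁ + n₂ − 2) × √(1/n₁ + 1/n₂).

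- 40 + 40: 1.9908 × 0.22361 = 0.445
- 35 + 35: 1.9955 × 0.23905 = 0.477
- 40 + 30: 1.9955 × 0.24152 = 0.482

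The interval is therefore wider by 0.477/0.445 = 1.07, about 7%, or by 0.482/0.445 = 1.08, about 8%. On the Decision Conflict Scale (0 to 100), the half-widths are:

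| Assumed SD (points) | 40 + 40 | 35 + 35 |
|---|---|---|
| 15 | 6.7 | 7.2 |
| 20 | 8.9 | 9.5 |
| 25 | 11.1 | 11.9 |

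**Step 3: power, for scale only.** From the noncentral t distribution with two-sided α = 0.05:

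| Split | Difference detectable with 80% power | Power at 0.5 SD | Power at 0.6 SD |
|---|---|---|---|
| 40 + 40 | 0.634 SD | 59.8% | 75.5% |
| 35 + 35 | 0.679 SD | 54.1% | 69.7% |
| 40 + 30 | 0.686 SD | 53.2% | 68.8% |

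The 80% level is a conventional yardstick chosen here. The article sets no power.

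**The case against.** The strongest reply is that the operative section leaves no doubt. Design and Settings gives the size of each phase, the duration of each phase, the total and the rationale, and these agree with one another. The abstract carries a lone total with no split, which looks like a figure that was not updated. That stands, and it is why 70 is the likelier error. It does not remove the contradiction: both sentences are current and describe the same phase, and a reader cannot be certain which number the authors intend.

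Two stronger readings are tempting, and the article supports neither.

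- A reader might infer that the study could stop at 35 per phase and still count as complete. A figure of 35 per phase appears nowhere in the article, and stopping there would breach the phase targets of 40 in Design and Settings.
- A reader might infer that the planned precision or power is undermined. None is planned. The size is set by feasibility, the methods describe exploring potential effects in order to inform a definitive trial, and the Discussion already warns that the small sample limits interpretation. The study is a small pilot at either number.

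It is also fair to say that a condensed article may leave an attrition allowance to the full protocol. Its absence is not the point here. What is wrong is that the article gives two totals.

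**Conclusion.** The inconsistency is real: 70 in the abstract against 40 + 40 = 80 in Design and Settings, with nothing to reconcile them. The number 80 is probably the plan, because the section that sets it is consistent throughout; the authors need to confirm it.

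The size of the problem is 10 encounters (12.5%). Under the assumed splits, the confidence interval would be about 7% to 8% wider at 70 than at 80. At the assumed differences of 0.5 and 0.6 SD, power would be roughly 6 to 7 percentage points lower. The outcome, the comparison and the significance level are unaffected, and no stated power is contradicted. This is a correction of a figure on which the study relies for judging recruitment, and not a flaw in its design.

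**What to change.** Confirm the intended total and give the same figure in the abstract and in Design and Settings.

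- If Design and Settings is the plan, change the abstract from 70 to 80 (40 + 40).
- Only if 70 was meant as the number expected to be evaluable out of 80 enrolled, say so explicitly in both places.

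Recruitment should then be reported against that single figure. A statement of expected precision is not needed to resolve the mismatch. The cost is a wording correction, with no extra patients and no change to the design or analysis.

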**Results:**

Interviews with cancer patients, oncologists, and health care providers (ie, nurses, nutritionists) as well as a literature review from phase I have been completed. The field testing is scheduled for April 2021 to August 2021, with the final revision scheduled for September 2021. The pre-post study of the DA and acceptance testing are scheduled to start in October 2021 and shall be finished in September 2022.

**Conclusions:**

A unique feature of this study is the development of a DA for patients with different types of advanced cancer, which covers a wide range of topics relevant for patients near the end of life such as forgoing cancer-specific therapy and switching to best supportive care.

**Trial Registration:**

ClinicalTrials.gov NCT04606238; https://clinicaltrials.gov/ct2/show/NCT04606238.

**International Registered Report Identifier (IRRID):**

DERR1-10.2196/24954

## Introduction

### Background

Patients with advanced cancer, when most standard therapies have been administered, are confronted with complex decisions about the further course of their treatment. They might face such decisions as (1) forgoing cancer-specific treatment and focusing on best supportive care or (2) off-label treatment within an individual treatment plan or possible inclusion in early clinical trials (ie, phase I and II studies).

Such decisions are complex and require the consideration of patients’ decision-making values and treatment preferences as well as weighing different factors such as patients’ quality of life, therapy side effects, and uncertainty about possible treatment outcomes [1,2]. We use the term decision-making values for the importance that patients place on the options’ positive and negative aspects when considering a specific decision. Treatment preferences refer to the degree to which each patient prefers each treatment option [3]. Treatment preferences (ie, regarding family involvement in decisions or the extent of participation in decision making) and patients’ decision-making values (ie, for quality or length of life) might differ considerably [3]. Current guidelines on advanced care planning [4] emphasize the importance of consideration and timely integration of patients' treatment preferences and decision-making values in decision making in advanced cancer [3,5,6].

Furthermore, compounding the decisional process is that, on the one hand, oncologists often avoid prognosticating and eliciting patients’ treatment preferences for or against anticancer therapy and decision-making values [5-9]; on the other hand, many patients tend to have an inaccurate perception of the curability of their cancer [5,10-13]. A multicenter international study conducted with 1390 patients with advanced cancer demonstrated that 55% of patients receiving palliative care thought that their cancer was curable [10]. The same is true of patients participating in clinical trials. Many of them tend to have therapeutic misconception. They misunderstand a trial’s purpose and express “unrealistic optimism” regarding its benefits [14-18]. A study with 301 cancer patients with gastrointestinal, gynecological, and lung cancers showed that more than 80% of patients in phase 1 clinical trials expected clinical benefits (ie, tumor shrinkage) and 10% even hoped for a cure [18].

Against this background, shared decision making (SDM), an approach based on patients’ engagement in the decisional process, becomes of particular importance in advanced cancer planning [11]. SDM has been increasingly advocated as it elicits patients’ decision-making values and treatment preferences. It permits informing patients about treatment benefits and harms and involving patients more actively in care planning, helping them weigh information based on their preferences [2].

Despite the fact that patients with advanced cancer might differ in their coping with disease [12], need for information, and preferred level of involvement in decisions [13,19], there is an urgent need to facilitate SDM and systematically support patients and oncologists in arriving at evidence-informed and value-congruent decisions as these decisions have a major impact on patients’ last months of life [2].

One of the existing possible ways to facilitate SDM is using patient decision aids (DAs). DAs are tools (pamphlets, videos, web-based or paper-based materials) that aim to help patients to participate in decision making. They provide information about different treatment options and patient-related advantages and disadvantages, help patients clarify their health care goals, and elicit and integrate their decision-making values in the decision-making process [20,21].

Various systematic literature reviews on DAs for people facing treatment or screening decisions demonstrated that the use of DAs can improve SDM, aligning decisions with the preferences of patients without negative impact on clinical outcomes. DAs have been shown to increase patients’ involvement in decision making in various clinical domains as well as to improve patients’ informed choices and to facilitate challenging discussions about goals of care and advanced care planning. Studies show that using DAs can contribute significantly to reducing decisional conflict and make patients feel more confident to make decisions [20,22-24]. The use of DAs has been shown to be associated with patients’ increased knowledge of treatment options [20]. Patients who used DAs had a more accurate risk perception and more realistic expectations of therapy outcomes [18,25,26]. For example, a study conducted with 40 hospitalized patients with advanced cancer demonstrated that a video DA reduced patients’ decisional uncertainty while increasing patients’ knowledge and readiness for palliative radiation therapy [27]. Furthermore, they could contribute to patients’ satisfaction with decisions and minimize patients and caregivers’ regret and blame on physicians [20,26,28-31].

However, many of the available DAs target patients considering therapy for early-stage cancer, cancer screening, or decisions about genetic testing and rarely target patients considering the management of advanced cancer [26,32-35].

There are only a few DAs for advanced cancer patients even though recommendations for their systematic development have been published [21]. Existing DAs are limited in their use by a certain type of cancer (ie, colorectal cancer or prostate cancer [36,37]) or target certain treatment scenarios (ie, participation in early phase clinical trials [2], use of standard systemic cancer therapies [38,39], or initial treatment after diagnoses [40]). To our knowledge, one patient communication aid in the Dutch language has been developed that targets clarification of patients’ preferences and encompasses a question prompt list that can be used by patients with advanced cancer regardless of tumor type when talking to their oncologist [11].

### Study Objectives

Against this background, we aim to develop a patient DA with a patient-centered design to support advanced cancer patients and their oncologists in decision making about anticancer treatment in situations where standard anticancer treatment lines have been exhausted. The DA will be aimed at a heterogeneous population of cancer patients, independently of cancer type as it will focus on situations that are generic for patients when standard treatment options are about to be exhausted. These decisions are typically similar for all cancer types and are about forgoing cancer-specific therapy and switching to best supportive care. The alternative is an additional tumor-specific treatment as off-label treatment, experimental individual treatment plan, or treatment within a clinical trial. With such a generic DA, we aim to facilitate routine initiation of the end-of-life discussions that still occur too late in the course of disease. Second, we aim to develop a clinically feasible implementation plan for the DA.

Furthermore, we aim to assess the acceptance and test potential effects of the developed DA on (1) oncologist-patient interaction (ie, satisfaction with the oncologist-patient interaction), (2) patient involvement in decision making, and (3) level of decisional conflict and uncertainties about choices.

### Conceptional Framework

The novelty of this study and the planned DA is that it targets patients with different types of advanced cancer in order to provide them with information and help them decide about the continuation or forgoing of tumor-specific therapy in clinical situations, in which there is no further standard tumor-specific therapy available but treatment is available as off-label treatment or part of a trial. Hence, the DA aims to facilitate SDM, which is essentially the communication of the best-available research evidence on benefits and harms of options and the clarification of patients’ treatment preferences in relation to this information [41]. Based on a consensus of experts in the field [41], SDM has been defined in terms of 3 broad phases: (1) team talk: work together, describe choices, offer support, and ask about patients’ goals; (2) option talk: discuss alternatives using risk communication principles; and (3) decision talk: get to informed preferences, make preference-based decisions.

The DA in our project is used to influence phase 1 of the SDM, which will probably affect the health care provider-patient communication in phases 2 and 3 as well. Based on the available body of randomized trials on clinical DAs [20], we primarily expect decreased patient decisional conflict and an increased feeling of being informed. Although the impact of DAs on professional performance seems limited overall, the use of the DA with patients with advanced cancer may also reduce intensive treatment. While we will measure quality of life in our study, we do not expect changes as a result of the use of the DA based on the available research evidence [20]. Given the practice-based character of the study, we did not specify and measure psychological factors and processes that may be affected by the DA, such as coping mechanisms.

## Methods

### Overview

We will use a systematic stepwise development process for the DA based on the International Patient Decision Aid Standards (IPDAS) collaboration guidelines, which are particularly relevant to “preference-sensitive” decisions [21,42]. The process will include the following key steps of DA development and testing: (1) establishing the informational basis for patients’ and health care providers’ decisional and information needs, (2) development and review of the DA by the interdisciplinary research group and presenting it in research colloquiums, (3) testing of the DA (design and field testing) with patients and health care providers (understandability, acceptance, usability, and feasibility testing) as well as usage instruction with health care providers, (4) pilot study in a pre-post design with baseline and intervention phases to evaluate the DA with regard to 3 objectives of feasibility and pilot research [43]: testing procedures, estimating recruitment and retention, and determining sample size. The first 2 objectives primarily relate to feasibility, while the third objective relates to the effectiveness of the intervention (the smaller the potential effects, the higher the sample size in a definitive trial needs to be). For the third objective, we have included patient-related outcomes and have planned to explore the potential effects of the DA in a pre-post comparison. The intervention phase will include user acceptance testing with oncologists and patients.

The model of the DA development process based on the model by Coulter et al [44] is presented in Figure 1.

